### Myocardial F-18 FDG PET/CT

4.3

Myocardial F-18 FDG PET/CT was performed within 2 days of each other. After an overnight fasting for at least 12 hours, an oral glucose of 10 to 50 g was given to the patients according to their serum glucose level. For diabetics, acipimox was administrated (500 mg; oral dose) before glucose loading. Insulin was intravenously administrated if the blood glucose level >9 mmol/L at 45 minutes after oral glucose administration with close monitoring of blood glucose. When the blood glucose level was appropriate, F-18 FDG (3 MBq/kg) was administered intravenously. Images were acquired 1 to 2 hours after tracer injection using a Biograph mCT 128 PET/CT scanner (Siemens Medical Solutions, Knoxville, TN) equipped with high-performance LSO PET crystals and a 128-slice CT. After a scout CT acquisition (120 kV, 10 mA) used for proper patients positioning, a CT transmission scanning (140 kV, 35 mA) was performed for attenuation correction and anatomical localization. Images were reconstructed using TrueX+TOFUltralHD reconstruction (21 subsets, 4 iterations). The Cedars software (Cedars-Sinai Medical Center, Los Angeles, CA) for phase analysis was applied on F-18 FDG PET/CT scans.

Nongated SPECT images were used for myocardial perfusion assessment by Quantitative Perfusion SPECT. Perfusion defect extent was expressed as a percentage of the whole myocardium area. Scar burden and myocardial viability were assessed by 2 experienced nuclear physicians. Segments with tracer uptake < 50% were considered transmural infarcted myocardium. F-18 FDG PET images were read in combination with rest SPECT images for myocardial viability assessment. The patterns of perfusion-metabolism mismatch and normal perfusion irrespective of F-18 FDG uptake signified viable myocardium whereas perfusion-metabolism match signified myocardial scar or nonviable tissue. The extent of viable myocardium and scar was expressed as percent of the LV area (%).

### CMR scanning

4.4

CMR imaging was performed within 2 days of each other. CMR imaging will be performed on 3.0 T whole-body scanner (MAGNETOM Verio, A Tim System; Siemens Healthcare, Erlangen, Germany). A 32-element matrix coil was activated for data collection. All images will be acquired using phased array surface coils during mild expiration and electrocardiographic triggering. Cine images will be acquired in the 4-, 2-chamber and contiguous short axis views using a steady state-free precession (SSFP) sequence. A bolus of 0.05 mmol/kg of gadolinium injected at 5 mL/s through a dedicated right antecubital vein. Ten minutes after the first gadolinium injection; perfusion imaging was repeated. A 2-dimensional phase-sensitive inversion recovery breath-hold sequence was used for LGE imaging. This acquisition was performed for at least 8 minutes (but no longer than 30 minutes) after the last administration of gadolinium.

## Endpoints

5

### Primary endpoint

5.1

The primary study endpoint of the SOS-comedy trial is changed to myocardial viability from baseline assessed with the use of PET/CT system during 12-month follow-up.

### Secondary endpoints

5.2

Major adverse cardiac events (MACEs) including all-cause mortality, cardiac mortality, first or recurrent acute MI, recurrent angina, target lesion revascularization (TLR), heart failure, and rehospitalization at 30-day, 6-month, and 12-month follow-up;The rates of target vessel revascularization, TLR, and stent thrombosis at 30-day, 6-month, and 12-month follow-up;Stroke incidence;Changes to LVEF assessed with the use of CMR and TTE;Changes to myocardial infarct size, left ventricular mass (LVM), cardiac output (CO), stroke volume (SV), maximum left ventricular ejection rate, maximum left ventricular filling rate, and maximum slope assessed with the use of CMR;Changes to left ventricular end-diastolic diameter (LVEDd), left ventricular end-systolic diameter (LVESd), and cardiac systolic function (E/A, E’/A’, Ea/Aa, EDT) assessed with the use of TTE;The number of compliant patients which defined as those who take predefined percentage (100%) of the treatment;The total cost of medical care;Number of guidewires, balloons, and stents used in the procedure;The volume of contrast used during the procedure;Type of the first guidewire and the final guidewire to cross the proximal lesion and the new devices used in the procedures;The special techniques used in the procedures.

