### Decision aid (DA)

4.1

As shown in Fig. 2, in the pilot trial of DA, the major benefits and risks for patients using both strategies are listed. Only options with the most concerns will be presented in the final version of the questionnaire, including outcomes, complications, costs, follow-up requirement, further revisualization, contrast-induced nephropathy, and radiation injury. With the DA, the clinicians introduce all major benefits and risks if CTO patients choose PCI or medication using the words such as “during the next 5 years, among 100 patients like you, 5 patients have a risk of myocardial infarction…”.

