## Sample size calculation

7

The main goal of this study is to estimate the improvement of myocardial viability associated with different treatment strategies evaluated by PET/CT. Thank you for your kind comments. We set the sample size by 2 means. First, at the time of study design and commencement, no studies examined the effect of PCI and/or OMT on myocardial viability in single-vessel CTO. Therefore, it is difficult to calculate a target number of patients that should achieve the primary endpoint. For this reason, we consulted with statisticians and set sample size to 200 patients according to previous studies on CTO, which is more than previous studies and feasible to realize. Second, retrospective data indicates that about 80% patients could reach the improvement rate of 5% by PCI, which indicates significant. Approximately 20% patients treated with OMT only can be improved more than 0.5%. We hypothesize that 40% patients’ myocardial viability of both groups could be improved significantly. A total of 131 patients is needed to reject the null hypothesis of no difference between groups (2-sided test *χ*^2^ test, power 90%, α=0.05). Allowing for a 15% drop-out rate, 151 patients will be recruited. Since this is a multicenter study, the sample size was enlarged to 200 patients.

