## Statistical analysis

8

Normally distributed continuous variables were presented as the mean ± SD, variables with a skewed distribution as the median together with interquartile range (IQR). Categorical variables are expressed as percentages. Changes in data measured by PET/CT, CMR, and TTE will be summarized by mean, standard deviation, minimum, median, and maximum. Differences between groups, including baseline characteristics, will be compared using a *t* test, Wilcoxon rank-sum test, or *χ*^2^ test. The correlation between treatment strategies and viable myocardium will be analyzed by liner regression analysis.

For the safety evaluation, the number and prevalence of MACEs will be calculated. The Kaplan–Meier method was used to illustrate the timing of events during follow-up in relation to treatment strategies and statistical assessment was performed with the log-rank test. The prognostic value of treatment strategies was assessed by investigating its relation with the composite outcome in Cox proportional-hazards analyses.

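### If cost is skewed, the stated rule summarises it by the median, which does not estimate the difference in mean (and so total) cost between PCI and OMT

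*Protocol article*

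**What the plan says.** Under Secondary endpoints, the Protocol article lists "The total cost of medical care" with no summary measure or test of its own. The Decision aid section names cost among the items put to patients ("including outcomes, complications, costs, follow-up requirement").

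The Statistical analysis section gives general rules:
- For normal variables: "Normally distributed continuous variables were presented as the mean ± SD".
- For skewed variables: "variables with a skewed distribution as the median together with interquartile range (IQR".
- For comparisons between groups, a list of tests: a t "test, Wilcoxon rank-sum test, or" a chi-square test, without saying which variable gets which test.
- One class of data is promised both mean and median: "Changes in data measured by PET/CT, CMR, and TTE will be summarized by mean, standard deviation, minimum, median, and maximum". Cost is not in that class.

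**The concern.** The endpoint is total cost. Mean cost per patient times the number of patients gives a total; a median or a rank sum does not. A rule that reports only the median for a skewed variable therefore answers a different question from the one the endpoint names.

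The mismatch matters most when the groups' cost distributions differ in shape, and here they may. PCI carries a procedure cost at the start for nearly every patient. OMT may be inexpensive for most patients and costly for those who are readmitted or later revascularized. A median hardly registers such a minority. At the least the size of the cost difference is misstated; in the extreme, the strategy reported as cheaper is the one that costs more.

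**Working it through.** The document gives no cost figure, so there is none to reproduce. All costs below are assumptions in arbitrary units. The simulations use 100 patients per group and two-sided 0.05. The 100 per group is half of the planned 200 ("the sample size was enlarged to 200 patients"); the groups form by choice and no ratio is stated.

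**Formula.** A lognormal cost with median M and log-SD s has mean M × exp(s²/2).

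**Set A: size of the gap.** PCI = 55 + lognormal(1.5, 0.5). OMT is a mixture: most patients at median 8 (log-SD 0.5), a fraction p in a tail at median T (log-SD 0.4).
- PCI mean = 55 + exp(1.5 + 0.125) = 60.1; PCI median = 55 + exp(1.5) = 59.5.
- OMT mean = (1 − p) × 8 × exp(0.125) + p × T × exp(0.08).
- OMT median with p = 0.2: the tail lies far above it, so it is the 0.5/0.8 = 62.5th percentile of the low-cost part, 8 × exp(0.5 × 0.319) = 9.4, whatever T is.

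| Tail | OMT mean | Mean gap (PCI − OMT) | Median gap (PCI − OMT) |
|---|---|---|---|
| 20% at 70 | 7.25 + 15.17 = 22.4 | 37.7 | 59.5 − 9.4 = 50.1 |
| 20% at 240 | 7.25 + 52.00 = 59.2 | 0.8 | 50.1 |

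The median gap is the same in both rows while the mean gap falls from 37.7 to about 1. In the second row Wilcoxon called OMT cheaper in all 2,000 simulated trials, whereas a Welch t test rejected in 6.6%. In the first row means and ranks agree that OMT is cheaper.

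**Set B: direction, with other distributions.** PCI is lognormal with median 60 and log-SD 0.25, so its mean is 60 × exp(0.031) = 61.9. OMT is lognormal with median 20 and log-SD 0.6, so its base mean is 20 × exp(0.18) = 23.9. A fraction p incurs an extra cost of median T and log-SD 0.5, which adds p × T × exp(0.125) to the mean. There were 1,000 simulated trials per row.

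| Tail | OMT mean (PCI 61.9) | Wilcoxon: OMT cheaper | Welch t: OMT cheaper | Welch t: OMT dearer |
|---|---|---|---|---|
| none | 23.9 | 100% | 100% | 0% |
| 10% at 100 | 35.3 | 100% | 99.6% | 0% |
| 20% at 150 | 57.9 | 100% | 12.1% | 0.3% |
| 25% at 200 | 80.6 | 99.9% | 0.1% | 29.9% |
| 30% at 200 | 91.9 | 97.5% | 0% | 70.8% |

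**When direction reverses.** In Set B, OMT is dearer on average once p × (mean extra cost) exceeds 61.9 − 23.9 = 38.0. At p = 0.20 the mean extra cost must exceed 38.0/0.20 = 190, about 3.1 times the PCI mean. If each tail patient's extra cost were one PCI (61.9), p would have to exceed 38.0/61.9 = 61%, and the OMT median would then lie in the tail too.

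**Shape is what matters.** With purely lognormal costs, medians 100 v 80 and equal log-SD of 0.5, medians and means rank the groups alike. With log-SDs of 0.3 and 1.0, the means are 104.6 v 131.9, and Wilcoxon significantly favoured the dearer group in 53% of trials.

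**The case against.** **The rule is partly inferred.** The article never says that cost is skewed and never assigns Wilcoxon to it; the t test, which compares means, is on the same list. A reader might infer that the plan fixes a median and Wilcoxon analysis of cost. It does not. What is explicit is median with IQR for any skewed variable, with no exception for cost; the step to Wilcoxon is only the usual reading.

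**An unseen document may treat cost separately.** It may, and the lack of a dedicated cost analysis in an article is no fault. The point is narrower: the general rule that is stated fits this endpoint badly.

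**The reversal depends on the inputs.** This stands. In Set A's units, an OMT patient who crosses over to PCI costs about 9 + 60 = 69. With 20% crossing over, mean OMT cost is 0.8 × 9 + 0.2 × 69 = 21 against 60, and both methods say that OMT is cheaper. Equal means would need (60.1 − 7.25)/0.2 = 264 per tail patient, over four times the PCI mean. The examples also give PCI no late-event tail, although the article counts target lesion revascularization, stent thrombosis and rehospitalization as outcomes. The cited comparison of 435 single-vessel CTO patients reports MACE in 16 OMT and 41 PCI patients (group sizes not given) and no significant difference after matching. Nothing there supports a costly tail confined to OMT. A reader might infer that the rule favours OMT almost by construction; the documents do not support that.

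**The stakes are limited.** Costs appear in the decision aid, but the article does not say that the trial's cost result will feed back into it. The primary endpoint and sample size are untouched.

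**Conclusion.** The concern holds in a conditional form. If cost is skewed, the stated summary is the median with IQR, which does not estimate the mean cost difference that the endpoint calls for. The usual companion test does not estimate it either.

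The more general consequence is a wrong size: a median gap of 50.1 where the mean gap is 37.7, with the direction unchanged. A wrong direction is possible but needs a sizeable OMT tail at several times the PCI cost, as in the 25% and 30% rows of Set B. With no tail, a small one, or one priced near a single PCI, means and ranks agree.

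These sizes rest on assumed distributions and equal groups of 100, not on trial data; skewness of cost is likewise an assumption, though a reasonable one. Severity is minor: a cheap improvement to one secondary endpoint.

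**What to change.** Exempt cost from the skewed-variable rule in the Statistical analysis section. State that cost is reported as the arithmetic mean 12-month cost per patient by strategy, with the mean difference and a non-parametric bootstrap 95% CI, or from a gamma model with log link. Either analysis should adjust for baseline characteristics because patients choose their group; an unadjusted mean difference would still be confounded. Give medians and IQRs as description only.

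The change takes a sentence or two of text and uses cost and baseline data that the trial already plans to collect. The price is a wider interval than the rank test suggests, because the mean carries the uncertainty of the expensive tail.

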## Safety monitoring

6

For the safety evaluation, the numbers and prevalence of adverse events including MACEs and stroke will be evaluated at each study visit. Stroke is defined as any new neurologic symptoms in association with signs of ischemia or hemorrhage in cranial computed tomography or magnetic resonance imaging.

## Sample size calculation

7

The main goal of this study is to estimate the improvement of myocardial viability associated with different treatment strategies evaluated by PET/CT. Thank you for your kind comments. We set the sample size by 2 means. First, at the time of study design and commencement, no studies examined the effect of PCI and/or OMT on myocardial viability in single-vessel CTO. Therefore, it is difficult to calculate a target number of patients that should achieve the primary endpoint. For this reason, we consulted with statisticians and set sample size to 200 patients according to previous studies on CTO, which is more than previous studies and feasible to realize. Second, retrospective data indicates that about 80% patients could reach the improvement rate of 5% by PCI, which indicates significant. Approximately 20% patients treated with OMT only can be improved more than 0.5%. We hypothesize that 40% patients’ myocardial viability of both groups could be improved significantly. A total of 131 patients is needed to reject the null hypothesis of no difference between groups (2-sided test *χ*^2^ test, power 90%, α=0.05). Allowing for a 15% drop-out rate, 151 patients will be recruited. Since this is a multicenter study, the sample size was enlarged to 200 patients.

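### The stated 131 patients and 90% power belong to a responder comparison that is not an endpoint of the trial, and 131 does not follow from the printed rates

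*Protocol article*

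**What the plan says.** Section 5.1 gives the primary endpoint as "changed to myocardial viability from baseline assessed with the use of PET/CT system during 12-month follow-up". It sets no cut-off for response, and neither does the Abstract. Section 4.3 fixes the scale: "The extent of viable myocardium and scar was expressed as percent of the LV area". Section 8 handles it as a continuous quantity: "Changes in data measured by PET/CT, CMR, and TTE will be summarized by mean, standard deviation, minimum, median, and maximum". The same section plans a linear regression relating viable myocardium to treatment strategy.

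Section 7 works with something else, the proportion of patients who improve:

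- For PCI, "retrospective data indicates that about 80% patients could reach the improvement rate of 5% by PCI".
- For OMT, "Approximately 20% patients treated with OMT only can be improved more than 0.5" per cent.
- A third rate, 40%, is attached to the hypothesis that "myocardial viability of both groups could be improved significantly".

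From these it states a total of 131 patients (two-sided chi-square test, 90% power, alpha 0.05), then 151 after a 15% drop-out allowance, then 200 because the study is multicentre. It also gives a separate basis for 200: previous CTO studies, advice from statisticians, and feasibility. Section 3 reports 240 enrolled by November 2017.

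**The concern.** A power statement is only meaningful for the endpoint and test it was computed for. Here it was computed for a binary outcome that appears in neither section 5.1 nor section 5.2, while the primary outcome is a continuous change. No mean change and no SD is given, so a reader cannot tell what difference in viable myocardium the trial can detect.

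The two planning rates are also not two values of one binary outcome as printed. One is the share of patients reaching 5%, the other the share exceeding 0.5%. A chi-square sample size needs the same event in both arms. The 40% rate could be an overall rate, an alternative for one arm, or something else; the text does not say.

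What is at stake is whether the quoted size and power can be relied on when the trial is reported.

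**Working it through.** **Inputs.** From section 7: rates of 80%, 20% and 40%; two-sided alpha 0.05; power 90%; stated total 131; drop-out 15%; final size 200. From section 3: 240 enrolled. The allocation ratio is not stated, because groups form by patient choice; 1:1 is assumed below and 1:2 is shown for range.

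**1. Can 131 be reproduced?** The usual formula per arm, with p̄ the mean of p1 and p2, is

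n = [1.960·√(2p̄(1−p̄)) + 1.2816·√(p1(1−p1) + p2(1−p2))]² / (p1 − p2)²

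- 80% v 20%: (1.960·√0.50 + 1.2816·√0.32)² / 0.36 = (1.386 + 0.725)² / 0.36 = 12.4, so 13 per arm, **26 in total**.
- 80% v 40%: (1.960·√0.48 + 1.2816·√0.40)² / 0.16 = (1.358 + 0.811)² / 0.16 = 29.4, so 30 per arm, **60 in total**.
- 40% v 20%: (1.960·√0.42 + 1.2816·√0.40)² / 0.04 = (1.270 + 0.811)² / 0.04 = 108.2, so 109 per arm, **218 in total**.

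With a continuity correction the totals are 32, 70 and 238. At 1:2, uncorrected, they are 30, 66 and 240. None is 131. The nearest match from the printed rates is a one-sided 40% v 20% comparison at 2:1, which puts 131 to 133 patients in one arm but 197 to 200 in total. Section 7 specifies a two-sided test and calls 131 the total.

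Read the other way, 131 patients at 1:1 give power above 99.9% for 80% v 20%, 99.9% for 80% v 40%, and 71% for 40% v 20%. None of these is 90%.

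**2. The drop-out step.** 131 × 1.15 = 150.7, which gives the stated 151. To keep 131 evaluable after losing 15%, 131 / 0.85 = 154.1, so 155. The final 200 exceeds both, so nothing turns on this.

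**3. What do the printed rates imply with one common cut-off?** Any patient above 5% is also above 0.5%, so the OMT rate at a common 5% cut-off is at most 20%. Against 80% for PCI, OMT rates of 20%, 10%, 5% and 1% need totals of 26, 18, 14 and 12.

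**4. What do they imply on the continuous scale?** Assume normal changes with equal SD, and read both cut-offs as absolute % LV. Then 80% above 5 puts the PCI mean at 5 + 0.84 SD, and 20% above 0.5 puts the OMT mean at 0.5 − 0.84 SD. The difference is 4.5 + 1.68 SD, which is more than 1.68 SD. If 0.5% should read 5%, it is 1.68 SD.

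**5. What can the trial detect on its stated endpoint?** For a two-group comparison of means at 1:1 and 90% power, the detectable difference in SD units is (1.960 + 1.2816)·√(4/N) = 6.483/√N.

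| Evaluable N | 1:1 | 1:2 |
|---|---|---|
| 131 | 0.57 SD | 0.60 SD |
| 170 (200 less 15%) | 0.50 SD | 0.53 SD |
| 200 | 0.46 SD | 0.49 SD |
| 240 | 0.42 SD | 0.44 SD |

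The row for 240 takes every enrolled patient as evaluable. With 15% lost, 240 × 0.85 = 204, and 6.483/√204 = 0.45 SD. The document gives no SD, so these cannot be turned into % LV.

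**The case against.** The strongest reply is that nothing has been shown to be too small. This stands. On the document's own rates the continuous difference would be at least 1.68 SD, against about 0.50 SD detectable with 170 evaluable patients. The size of 200 also has its own basis in precedent and feasibility, and enrolment has passed it. A reader might infer from the mismatch that the trial is underpowered; the documents do not support that.

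A reader might also infer that outcomes will be judged at 5% in one arm and 0.5% in the other, which would bias the comparison. No section says so. Section 7 quotes these figures as planning data, section 8 contains no responder rule, and 0.5% may simply be a slip for 5%. Whether the improvement is absolute or relative is not defined either. Any calculated bias would describe an analysis that nobody has planned.

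Nor does section 8 offer three competing tests for the primary endpoint. Its t test, Wilcoxon and chi-square tests follow a description of normal, skewed and categorical variables and read naturally as a list by variable type. Leaving the assignment of a test to a fuller document is ordinary in an article. The linear regression on viable myocardium is already planned.

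What these replies leave untouched is that section 7 attaches a size and a power to an undefined endpoint, and that the size does not follow from its own inputs.

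**Conclusion.** The point holds as a fault in the stated justification. The 131 patients and 90% power refer to a responder proportion outside the endpoint list, with cut-offs that differ between arms as printed, and do not apply to the continuous change named as primary. The figure of 131 is not reproduced from 80%, 20% and 40%: the two-sided totals are about 26, 60 and 218 at 1:1, and neither a continuity correction nor a 1:2 split brings any of them to 131.

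If 0.5% is a misprint for 5%, the difference in cut-offs disappears, but the mismatch with the continuous endpoint and the failure to reproduce 131 both remain.

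The totals rest on the normal approximation and an assumed allocation ratio. The detectable differences rest on the same ratio and ignore both the baseline covariate and any further adjustment for self-selected groups. No shortfall in power is shown.

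**What to change.** - In sections 5.1 and 8, name the 12-month minus baseline change in viable myocardium (% LV) as the primary outcome, analysed by the linear regression already planned with baseline viability added as a covariate. No gain in precision should be promised for this: the usual variance formula assumes balanced baselines, which groups formed by patient choice need not have.
- In section 7, replace the 131 patients and 90% power with the detectable difference for that outcome: at 90% power and 1:1, about 0.50 SD with 170 evaluable, 0.46 SD with 200 and 0.42 SD with 240. State the assumed SD and its source, and use the actual split and evaluable number once known. Precedent and feasibility can stay as the reason for 200.
- If a responder rate is kept, make it secondary with one threshold for both arms, stated as absolute or relative.
- Reconcile the 5% and 0.5% figures, and explain or remove the 40%.

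The cost is rewording in three sections. No new data or patients are needed. With 240 already enrolled, the revised section 7 should say that it describes the precision of the achieved sample and was written after recruitment.

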## Interventions

3

This study will be conducted in accordance with the Declaration of Helsinki and with the approval of the ethical committees of the 4 participating institutions. Recruitment commenced on October 20, 2015, and as of November 2017, 240 patients have been enrolled. The trial is registered under www.clinicaltrials.gov: NCT02767401.

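### The 131 patients said to give 90% power do not follow from the response rates stated beside them, and those rates are defined on two different thresholds

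*Protocol article*

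**What the plan says.** Section 7 (Sample size calculation) gives two grounds for the size. The first is that no earlier study had examined this question in single-vessel CTO, so a target was hard to calculate. The authors therefore took 200 from previous CTO studies and from what was feasible.

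The second ground is a calculation. Its inputs are:

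- PCI: "retrospective data indicates that about 80% patients could reach the improvement rate of 5% by PCI".
- OMT: "Approximately 20% patients treated with OMT only can be improved more than 0.5" per cent.
- A third rate, 40%, attached to the statement that "myocardial viability of both groups could be improved significantly".
- A two-sided chi-square test with "power 90%, α=0.05".

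The result is "A total of 131 patients is needed to reject the null hypothesis of no difference between groups". Then: "Allowing for a 15% drop-out rate, 151 patients will be recruited". The section next enlarges the number to 200 because the study is multicenter.

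Section 3 (Interventions) reports that "as of November 2017, 240 patients have been enrolled". The PCI:OMT ratio is not stated; the Abstract says that groups follow the patient's choice.

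**The concern.** The article prints the rates, the test, the significance level, the power and the resulting number together, so the calculation can be checked on the page. Rates of 80% and 20% differ by 60 percentage points, and a difference that large needs a few dozen patients, not 131. The 40% fits no obvious role: if it applies to each group, there is no difference to detect. The two response rates also use different cut-offs, 5% and 0.5%, so no single binary endpoint is being compared.

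This is the only power statement in the article. As it stands, a reader cannot tell which difference the trial was sized to detect.

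**Working it through.** **Inputs from section 7.** Two-sided alpha 0.05 (z = 1.960), power 90% (z = 1.282), chi-square test of two proportions, rates 80%, 20% and 40%, stated total 131, drop-out 15%. **Assumption:** equal arms unless noted, because no ratio is given.

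**Formula (pooled variance, per arm).** With p̄ the mean of p1 and p2:

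n = [1.960·√(2p̄(1−p̄)) + 1.282·√(p1(1−p1) + p2(1−p2))]² / (p1 − p2)²

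**Trying to reproduce 131**

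- 80% v 20%: (1.386 + 0.725)² / 0.36 = 12.4, so 13 per arm, 26 in total (32 with continuity correction).
- 80% v 40%: (1.358 + 0.811)² / 0.16 = 29.4, so 30 per arm, 60 in total (70 corrected).
- 40% v 20%: (1.270 + 0.811)² / 0.04 = 108.2, so 109 per arm, 218 in total (238 corrected).
- 40% in each group: the difference is zero, so no sample size exists.
- 40% overall: 0.8p + 0.2(1 − p) = 0.4 gives p = 1/3, a 1:2 PCI:OMT split. For 80% v 20% at that split the total is 30 (36 corrected).

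Unpooled and arcsine variants do not help: for 80% v 20% they give 9.3 and 12.7 per arm. The nearest match at the stated settings is 60% v 40%, at 130 per arm, but 60% appears nowhere and the text says 131 is a total. For 40% v 20%, a total of 128 appears only with a one-sided test and 80% power, against the text. For 80% v 20%, a total near 131 needs an allocation of roughly 1:15 with continuity correction (128) or 1:20 without (126).

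**What 131 would give (65.5 per arm)**

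Power = Φ{[|p1 − p2|·√n − 1.960·√(2p̄(1−p̄))] / √(p1(1−p1) + p2(1−p2))}

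- 80% v 20%: (0.6 × 8.093 − 1.386) / 0.566 = 6.13, power above 99.99%.
- 40% v 20%: (0.2 × 8.093 − 1.270) / 0.632 = 0.55, power about 71%.

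**The two thresholds.** If 20% of OMT patients improve by more than 0.5%, at most 20% can reach 5%. If 80% of PCI patients reach 5%, at least 80% exceed 0.5%. On either common threshold the implied gap is therefore at least 60 points, so using one threshold does not bring the requirement closer to 131.

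**Drop-out step.** 131 × 1.15 = 150.65, which is the stated 151. Allowing for 15% loss means 131 / 0.85 = 154.1, so 155.

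**Detectable difference at realistic sizes (illustration).** Assume a pooled response rate of 40%, 90% power and two-sided 5%. Evaluable numbers are 200 × 0.85 = 170 and 240 × 0.85 = 204.

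| Evaluable | 1:1 | 1:3 PCI:OMT (assumed) |
|---|---|---|
| 170 | 24 points | 28 points |
| 204 | 22 points | 26 points |

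**The case against.** The strongest reply is that 131 does not determine the size of the trial. Section 7 arrives at 200 from precedent and feasibility independently of the calculation, and deleting 131 would leave 200 in place. For the stated 80% and 20% the error is also in the safe direction, since 131 is about five times what those rates need. All of this stands, and it limits the point to the accuracy of the power statement. It does not make that statement right.

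Three stronger readings are tempting, and the article does not support them.

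- **That the trial is underpowered.** Under 80% v 20% it is not. Even under 40% v 20% at 1:1, 200 patients give about 88% power and 170 evaluable about 82%.
- **That enrolment beyond 200 was driven by the data.** No interim look or outcome-based decision is described. Since 240 less 15% is 204, recruiting to keep about 200 evaluable is an equally available explanation, though the article does not say that either.
- **That a null result could not be interpreted.** A completed trial is read from its estimate and confidence interval, not from its planning calculation.

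The drop-out slip is four patients and is overtaken by the move to 200. It is a side note only.

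**Conclusion.** The point holds as a false power statement, not as an undersized trial. No reading of the stated rates, at the stated test, alpha and power and with a plausible allocation, gives a total of 131. The figure is about five times too large for 80% v 20%, about twice too large for 80% v 40%, and well short for 40% v 20%. The rates themselves are not defined on one endpoint.

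The totals assume equal arms except where a ratio is shown. The detectable differences also rest on an assumed pooled rate of 40% and, in one column, an assumed 1:3 split; neither of these is given as a design value in the article.

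The gap between the stated size of 200 and the 240 enrolled is 40 patients (20%). It is real and unexplained, but it is a separate and minor matter.

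**What to change.** Reword section 7 as follows:

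1. Define response by one improvement threshold, applied to both groups, before quoting any rates.
2. Delete 131, 151 and the associated 90% power claim, or replace the inputs with ones that reproduce them. Do not substitute a fresh calculation from 80% v 20% while the two rates sit on different thresholds.
3. Keep precedent and feasibility as the stated basis for the size.
4. Give the detectable difference, or the half-width of the confidence interval, at the number enrolled, net of 15% loss and at the actual PCI:OMT split.
5. If a drop-out step is kept, use n / (1 − 0.15), which turns 131 into 155.
6. Reconcile the 200 in section 7 with the 240 in section 3 in one sentence.

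The cost is a rewritten section. No extra patients are needed.
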